### Participant timeline {13}

**Table Tabb:** 

**Participant timeline**	
**Outpatient clinic**	
Patient is provided with study information	
**Pre-surgery hospital admission**	
Written informed consent	
Baseline blood values are collected (from a routine preoperative blood sample)	
Baseline PROMs (WHODAS-12, TOPICS-SF, RDS) are assessed	
**Surgery**	
Patient is routinely admitted to the ICU after surgery	
**Postoperative day 1**	
Blood sample (iron status, ret Hb count)	
Definite inclusion in case of IDA	
Randomization	
Intervention:	
Group A: IVI	Group B: placebo
**Hospital discharge (± 5 days postoperative)**	
Blood sample (ret Hb count, Hb level)	
**90 days after surgery**	**90 days exploratory endpoints**
Follow-up PROMs (WHODAS-12, TOPICS-SF, RDS)	Results from the functional tests (steep-ramp/6-min walk test) Hb level

### Sample size {14}

In the previously conducted AGE cohort (ClinicalTrials.gov Identifier NCT02535728) studying a similar patient population, the mean WHODAS 2.0 score for CABG and AVR patients after 3 months was 12% points with a standard deviation (SD) of 15% points. For an expected effect size, a mean difference in WHODAS 2.0 score of 5% points or more between the treatment and placebo groups was chosen. This difference in WHODAS 2.0 score is consistent with a clinically relevant change in disability [18]. We based our sample size estimate on the most conservative (largest) standard deviation, which was 15% points. To detect a mean difference in WHODAS 2.0 score of 5% points at 90 days using a two-tailed unpaired *T*-test with a two-sided significance level of 5% and a power of 80% with equal allocation to two arms would require 142 patients per treatment group. Taking into account a loss to follow-up margin of 10%, we aim to include a total cohort of 310 patients. Calculations were performed using R version 3.6.1—© 2019–07-05, R, Inc., for Windows.

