**Methods:**

This is a randomized placebo-controlled double-blind multi-centre trial. In total, 310 patients aged ≥ 70 years with moderate IDA on postoperative day 1 (haemoglobin 85–110 g/L and ferritin concentration < 100 μg/L or iron saturation < 20%) after uncomplicated elective cardiac surgery (aortic valve repair or coronary artery bypass graft surgery) will be included. Patients will be randomly allocated to receive either IVI (ferric derisomaltose) or placebo (sodium chloride 0.9%) on postoperative day 1 in a 1:1 ratio, stratified by centre and type of cardiac surgery. The primary outcome is disability measured by the 12-item World Health Organization Disability Assessment score 2.0 after 90 days. Secondary outcome measures are the number of postoperative red blood cell (RBC) transfusions, change in reticulocyte haemoglobin content (pg) from randomization to hospital discharge, Hb levels at discharge, hospital complications, dyspnoea (assessed with the Rose Dyspnoea Scale) and health-related quality of life (HRQL) (assessed with The Older Persons and Informal Caregivers-Short Form (TOPICS-SF) questionnaire) after 90 days and days alive and out of hospital after 90 days. Lastly, the functional outcomes (e.g. steep ramp or 6-min walk test) and Hb level after 90 days will be assessed as an exploratory endpoint.

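### Minor, wrong as written: 310 patients do not carry the stated 10% loss margin; they allow about 8.4% before falling below the 284 the plan says it needs

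*Protocol article*

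**What the plan says.** The Sample size {14} section of the protocol article fixes every input. The target effect is given by "To detect a mean difference in WHODAS 2.0 score of 5% points at 90 days". The SD is "the most conservative (largest) standard deviation, which was 15% points". The test and error rates are set out as "using a two-tailed unpaired *T*-test with a two-sided significance level of 5" per cent, with "a power of 80% with equal allocation to two arms". From these the section concludes that the trial "would require 142 patients per treatment group", which is 284 in total.

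The next sentence turns this into the recruitment target: "Taking into account a loss to follow-up margin of 10%, we aim to include a total cohort of 310 patients". No inflation formula is given. The abstract repeats the target: "In total, 310 patients aged ≥ 70 years with moderate IDA on postoperative day 1".

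**The concern.** A loss margin has one purpose: if the stated fraction of patients is lost, the number required should still be there. Here it is not. The shortfall shows from two consecutive sentences with no outside assumption.

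What is at stake is the accuracy of a statement more than the strength of the trial. The 310 is the headline target, and this paragraph is its only justification in the article. Later reports are likely to cite it as the basis for 80% power with 10% attrition. Attrition between 8.4% and 10% would look as if it were within plan while leaving fewer patients than the plan calls necessary.

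**Working it through.** **Inputs**, all from Sample size {14}: difference 5 points, SD 15 points, two-sided alpha 0.05, power 0.80, 1:1 allocation, 142 per group, 10% loss, 310 in total.

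**Step 1. Reproduce 142 per group.**
- Normal approximation: n = 2 × [SD × (z for 1 − α/2 + z for power) / difference]² = 2 × [15 × (1.960 + 0.842)/5]² = 141.28, rounded up to 142. The plan's figure is reproduced.
- Exact solution for the t-test (noncentral t, standardised difference 5/15 = 0.333): 142.25 per group, so 143 if rounded up. Power is 79.93% at 142 per group and 80.21% at 143.

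The rest uses the plan's own 142, that is 2 × 142 = 284 evaluable patients.

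**Step 2. Apply the stated loss to the stated target.**
- 310 × (1 − 0.10) = 279.
- 284 − 279 = 5 patients short.

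**Step 3. Ask how 310 could arise.**
- Dividing by the retained fraction: 284/0.90 = 315.6, so 316.
- Adding 10% to the requirement: 284 × 1.10 = 312.4, so 313.
- Starting from 143 per group: 286/0.90 = 317.8, so 318.

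310 lies below all three. It is 6 patients below 316 (6/316 = 1.9%). It looks like a rounded figure, but rounded downwards.

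**Step 4. Find the loss that 310 does allow.**
- To keep 284: 310 − 284 = 26 patients; 26/310 = 8.4%.
- To keep 286: 310 − 286 = 24 patients; 24/310 = 7.7%.
- The stated 10% margin corresponds to 31 patients.

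**Step 5. Size the consequence at 10% loss.** With 279 analysed (140 and 139), difference 5 and SD 15, the noncentral t gives 79.2% power. The difference detectable with 80% power is 5.05 points instead of 5.00.

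**Step 6. See what baseline adjustment could return.** ANCOVA multiplies the residual SD by about √(1 − r²), where r is the correlation between baseline and 90-day WHODAS-12. The document does not give r, so the values here are assumptions. With 279 analysed:

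| Assumed r | Power for 5 points |
|---|---|
| 0 | 79.2% |
| 0.14 | 80.0% |
| 0.3 | 82.8% |
| 0.5 | 89.3% |

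A weak correlation is enough to close the gap.

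**The case against.** The strongest reply is that the discrepancy is too small to matter. A loss of 0.8 points of power and a shift of 0.05 in the detectable difference are less than the inputs can resolve. The SD is given as a whole number; any value from 14.5 to 15.5 would round to 15, and over that range the exact requirement runs from 133 to 152 per group. The section gives no inflation formula, and 310 is within 0.8% of 312.4, so it can be read as a rounded recruitment aim.

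Other parts of the protocol also help. The statistical methods section {20a} plans an ANCOVA with baseline WHODAS-12 and haemoglobin. The missing data section {20c} keeps all randomised patients in the analysis with multiple imputation. The outcomes section {12} scores death as full disability, so a death need not be a lost outcome.

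Most of this stands as an argument about weight, and it rules out two stronger readings that a reader might infer.

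- **That the trial is underpowered.** The documents do not support this. The shortfall is under one point of power for an unadjusted test, before any gain from the planned adjustment.
- **That 142 was itself wrongly rounded down.** This depends on the method. The normal approximation rounds up to 142; only the exact t solution asks for 143. The text names a t-test, so 143 is a fair preference, but it is worth one patient per group and the main point does not need it.

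What the reply cannot do is make the sentence correct. The section rests its claim on an unadjusted t-test, takes no credit for adjustment or imputation, and adds a margin precisely because it treats lost patients as needing cover. Even adding 10% to 284 gives more than 310.

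**Conclusion.** The stated loss tolerance is wrong on the document's own figures. With 284 evaluable patients required, 310 allows 8.4% loss and not 10%; a 10% margin needs 316. If the full 10% is lost, power by unadjusted t-test is 79.2% for a 5-point difference.

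This is a minor correction. It rests only on the inputs stated in the sample size section and on loss meaning a patient without an evaluable 90-day score. The ANCOVA may recover the shortfall, but by how much depends on a correlation that the document does not report, and the effect of multiple imputation cannot be quantified from it. The design, the recruitment target and the analysis need not change.

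**What to change.** Keep 310 and restate the sentence, for example:

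> An unpaired t-test requires 142 patients per group (284). Randomising 310 allows about 8% loss to follow-up; at 10% loss 279 remain, giving about 79% power for a 5-point difference by unadjusted t-test.

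Optionally, add that the exact t solution is 142.25 per group, so 143 if rounded up, which brings the loss tolerance to 7.7%; the normal approximation gives 142.

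The cost is one sentence and a slightly less favourable stated margin. If the sponsor prefers to keep the 10% claim, the target has to read 316 (318 from 143 per group), which means 6 to 8 more patients. The size of the effect does not call for that.

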### Recruitment {15}

Patients will be recruited at the preoperative assessment outpatient clinic of the participating hospitals by providing them with oral information and folders with study information.

## Assignment of interventions: allocation

### Sequence generation {16a}

Via a computer-generated randomization (randomization list will be generated using R version 3.6.1—© 2019–07-05, R, Inc., for Windows), patients will be randomized, stratified by hospital site and surgical intervention (AVR or CABG).

### Concealment mechanism {16b}

After the inclusion of the patient, the randomization and preparation of the trial medication will be overseen by a clinical pharmacist. Both participant and researcher will be blinded for the trial medication. As the ferric derisomaltose solution is brown and the placebo solution is colourless, the infusion bags and lines will be light-protected in order to prevent identification of the investigational product. The study medication will be administered through the central venous line, which is placed in the jugular vein in the neck and therefore out of sight for the patient. The patient’s general practitioner will be informed with regard to the study participation of the patient.

### Implementation {16c}

After signing the informed consent, research personnel that are not blinded for the allocation treatment will enrol the patients and use REDCap (VanderBilt University) to allocate the patient to one of the study arms. The clinical pharmacist will receive an allocation list that is automatically generated by REDCap (using an allocation sequence that was generated prior the trial by a member of the research team (RS)) with patients’ study IDs and corresponding treatment allocation and will prepare the appropriate trial medication.

## Assignment of interventions: blinding

### Who will be blinded {17a}

The members of the research team that will assess the outcome and analyse the data, as well as the patients will be blinded for the allocated intervention.

### Procedure for unblinding if needed {17b}

In the case of a suspected unexpected serious adverse reaction (SUSAR), the principle investigator is permitted to request a code break for the unblinding of the intervention allocation. The clinical pharmacist will perform the code break.

## Data collection and management

### Plans for assessment and collection of outcomes {18a}

Data will be derived from electronic patient records and collected with an electronic case report form (eCRF) using REDCap. Laboratory tests are performed by the clinical laboratory. Patients can fill out the baseline and follow-up questionnaires either digitally (the answers will be directly saved in REDCap) or on paper. If patients fill out the questionnaires on paper (Supplementary file 1), a member of the research team will enter the information manually into REDCap. For the exploratory endpoints, the results from functional tests (steep ramp or 6-min walk test) measured by the physical therapist as part of routine postoperative care are requested. In addition, laboratory results (i.e. Hb level if available) from outpatient visits for postoperative follow-up with the treating cardiologist are requested as an exploratory endpoint. All research personnel will be trained in the study requirements. All data outcome definitions are reported in a data management manual and a codebook, ensuring that the collected data is standardized.

### Plans to promote participant retention and complete follow-up {18b}

The patients will receive extensive information about the study set-up and requirements during the recruitment. The importance of completion of follow-up will be stressed. After 90 days, the patients are asked to fill out an electronic questionnaire (if possible) in REDCap. REDCap automatically generates reminders if patients do not respond to the request to fill out the questionnaire. If patients are not able to fill out the questionnaire electronically, the questionnaires will be sent by mail with a prepaid return envelope. Throughout the follow-up period, the researchers will check responses and if necessary contact patients for completion of their follow-up.

### Data management {19}

All data will be collected by the investigators and handled in a study database (REDCap) that is protected by two-factor authentication and only accessible to investigators of the study. REDCap is a secure web application for building and managing databases. To avoid erroneous values, a data range will be provided for all continuous data values. Questionnaires will be either filled out electronically by the patient in REDCap or entered manually by the investigators. Informed consent and end-of-trial dates will be recorded in the electronic patient dossier and signed paper forms will be stored within the hospitals in a locked cabinet. All changes to the raw data in REDCap are automatically recorded. All steps taken in the analysis will be documented in R (version 3.5.1—© 2018–07-02, R, Inc., for Windows). The dataset will be kept for 15 years.

### Confidentiality {27}

Patients will be assigned a unique study ID that is comprised of 2 letters (AN) and 3 digits (AN001, AN002, etc.). Personal information from study subjects will be untraceable from this study ID. A file containing the surname, date of birth and the corresponding study ID of all study patients will be safeguarded on a secure, password-protected hard drive on a hospital computer by the principal investigator of each participating hospital. All patient information will be processed according to the EU General Data Protection Regulation and the Dutch Act on Implementation of the General Data Protection Regulation (AVG).

### Plans for collection, laboratory evaluation and storage of biological specimens for genetic or molecular analysis in this trial/future use {33}

Not applicable. No biological specimens are collected.

## Statistical methods

### Statistical methods for primary and secondary outcomes {20a}

Data will be analysed using R statistics (version 3.5.1—© 2018–07-02, R, Inc., for Windows). Descriptive statistics will be calculated for all study parameters. Continuous data will be described as mean (+ standard deviation) and median (+ interquartile range) for normally and non-normally distributed data, respectively. Categorical variables will be described as numbers and percentages. The effect of IVI therapy on the primary and secondary endpoints will be analysed with ANCOVA and logistic regression analysis. All analyses are performed according to the intention-to-treat principle. Two-sided *P* values of 0.05 or less will be considered statistically significant.

Baseline characteristics will be described per treatment arm as percentages, means (± SDs) or medians (IQRs) as appropriate. The primary outcome, disability as measured by WHODAS-12 scores after 90 days will be compared between the two groups with the independent Student’s *t* test or Wilcoxon rank sum test, depending on the distribution of the data. Thereafter, to evaluate the effect of IVI on the primary outcome, an ANCOVA analysis will be performed with an adjustment for baseline Hb levels and WHODAS-12 scores. Effect estimates are presented as *β* with accompanying 95% confidence intervals (CI). New disability, defined as an increase in the WHODAS score ≥ 5% from baseline, will be compared between the two treatment groups by logistic or Poisson regression analysis and expressed with odds ratio (OR) or relative risks (RR), if appropriate. For the secondary outcomes, the difference in dyspnoea from baseline, assessed with the RDS, difference in Hb from baseline, difference in HRQL from baseline and number of red blood cell transfusions will be summarized descriptively and compared between the treatment groups with the independent Student’s *t* test or Wilcoxon rank sum test, depending on the distribution of the data. The difference in median days alive and out of the hospital at 90 days between the treatment groups will be analysed with the Wilcoxon rank sum test. The effect of IVI on secondary outcomes will be evaluated with ANCOVA analysis. Postoperative complications will be summarized by frequency and percentage and compared in the treatment groups with logistic regression analysis or Poisson regression analysis. As an exploratory endpoint, the results from functional capability tests (steep-ramp or 6-min walk test) after 90 days will be evaluated if available. The effect of postoperative IVI on functional capability tests will be evaluated with logistic or linear regression analysis, where appropriate. Another exploratory endpoint is a difference in Hb level after 90 days. The independent Student’s *t* test or the Wilcoxon rank sum will be used to compare Hb levels between the two treatment arms and linear regression analysis will be performed to evaluate the effect between the groups.

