### Outcomes {12}

The primary endpoint is the difference in median disability scores as measured by the 12-item World Health Organization Disability Assessment score 2.0 (12-item WHODAS 2.0) 90 days after elective cardiac surgery, between the two treatment arms. The 12-item WHODAS 2.0 is a validated questionnaire for the assessment of postsurgical disability in the following domains: communication, mobility, self-care, interacting with other people, taking care of housework and participating in the community. A disability score is calculated ranging from 0% (no disability) to 100% (fully disabled, including death). The difference in the proportion of patients with new disability between the two treatment arms is a secondary endpoint, defined as an increase in the 12-item WHODAS 2.0 score ≥ 5% at day 90 compared to the preoperative assessment (baseline) [18]. Other secondary endpoints are the difference in the median number of red blood cell (RBC) transfusion administered during hospital stay, the median change in reticulocyte haemoglobin content from POD 1 to hospital discharge, median Hb levels at discharge, proportion of in-hospital complications, median days alive and out of the hospital after 90 days, median score regarding dyspnoea symptoms after 90 days (assessed with the Rose Dyspnoea Scale (RDS)) and median HRQL scores (assessed with The Older Persons and Informal Caregivers-Short Form (TOPICS-SF) questionnaire) after 90 days. Lastly, we will consider functional outcomes (e.g. steep ramp or 6-min walk test) and median Hb levels after 90 days, as exploratory endpoints.

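### The primary comparison is described as a difference in medians, a t-test or Wilcoxon test, and an ANCOVA mean difference, and the protocol does not say which one decides

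*Protocol article*

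**What the plan says.** Four places in the protocol article bear on the primary comparison.

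- **Outcomes {12}:** "The primary endpoint is the difference in median disability scores", on the 12-item WHODAS 2.0 at 90 days. The scale runs from 0 to 100, with death placed at the top.
- **Sample size {14}:** "To detect a mean difference in WHODAS 2.0 score of 5% points at 90 days" by a two-sided unpaired t-test at 5% with 80% power needs 142 per arm. The planning values are mean 12 and SD 15.
- **Statistical methods {20a}, general paragraph:** "The effect of IVI therapy on the primary and secondary endpoints will be analysed with ANCOVA and logistic regression analysis". The significance rule is that P "values of 0.05 or less will be considered statistically significant"; it is not attached to a particular analysis.
- **Statistical methods {20a}, primary outcome:** the arms are first compared by a t-test or a Wilcoxon test. The choice between them, and the step that follows, are put this way: "depending on the distribution of the data. Thereafter, to evaluate the effect of IVI on the primary outcome, an ANCOVA analysis will be performed". The ANCOVA covariates are Hb and WHODAS at baseline, and the effect is reported as β with a 95% confidence interval.

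**The concern.** The trial has one confirmatory question, and its endpoint, sample size and analysis are not stated in the same terms. The endpoint is a median contrast, the sample size rests on an unadjusted mean contrast, and the analysis is an unadjusted test of one of two kinds followed by an adjusted mean contrast. No sentence ranks the unadjusted test against the ANCOVA.

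If the two give results on opposite sides of 0.05, the protocol does not say what would be concluded. A favourable result from either could then be presented as the primary finding, and a reader could not check that the choice was made independently of the results.

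**Working it through.** **1. The plan's own figure.** From {14}: difference 5, SD 15, two-sided 5%, power 80%.

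n per arm = 2 × (1.960 + 0.842)² × 15² / 5² = 141.3, rounded up to 142. This matches the protocol. Exact t-test power at 142 per arm is 79.9%. The stated power is therefore right for the test to which {14} ties it.

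**2. Is the t-test branch likely to be used?** A normal distribution with mean 12 and SD 15 puts Φ(−12/15) = Φ(−0.8) = 21% of scores below 0, where no WHODAS score can lie. The scores must be right-skewed, and deaths at 100 add to this. A choice made on the distribution therefore probably leads to the Wilcoxon test. {20a} gives no rule for the choice, so this is likely rather than certain.

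**3. Does any named method estimate a difference in medians?** The t-test and the ANCOVA contrast means. The Wilcoxon test compares whole distributions and corresponds to a difference in medians only if one arm is a pure shift of the other. A pure 5-point shift cannot hold for scores within 5 points of the floor. No named analysis therefore generally targets the endpoint as {12} defines it.

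**4. Error rate of the t-test/Wilcoxon choice alone.** Null trials were simulated with 142 per arm: 8,000 runs per setting, normal or gamma scores with mean 12 and SD 15, and the choice made by a Shapiro-Wilk test. The score shapes and the selection rule are assumptions. The chosen test rejected in 4.8% to 5.4% of runs, so there is no material inflation.

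**5. Error rate if either the unadjusted test or the ANCOVA may count.** Let ρ be the correlation between baseline and day-90 WHODAS. The protocol gives no value, so 0.3, 0.5 and 0.7 are assumed. Under the null, the unadjusted and adjusted z statistics are approximately bivariate normal with correlation √(1 − ρ²).

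| ρ (assumed) | √(1 − ρ²) | P(either \|z\| > 1.96) | P(both \|z\| > 1.96) |
|---|---|---|---|
| 0.3 | 0.954 | 6.4% | 3.6% |
| 0.5 | 0.866 | 7.3% | 2.7% |
| 0.7 | 0.714 | 8.3% | 1.7% |

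The last column follows from the third: 5% + 5% − P(either). The simulation gave 6.7% to 7.9% (normal scores) and 7.6% to 9.1% (gamma scores) for the either-counts reading, and 1.4% to 3.8% if both must be significant.

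**6. How often would the two analyses disagree?** With a true 5-point mean difference (3,000 runs per setting, same assumptions), the chosen unadjusted test and the ANCOVA fell on opposite sides of 0.05 in 6.5% to 18.8% of simulated trials.

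**7. Power if ANCOVA is the one analysis.** The residual SD is 15√(1 − ρ²), and power = Φ(5 / [SD × √(2/142)] − 1.96).

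| ρ (assumed) | Residual SD | Power at 142 per arm |
|---|---|---|
| 0.3 | 14.31 | 83.8% |
| 0.5 | 12.99 | 90.0% |
| 0.7 | 10.71 | 97.6% |

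These figures make no allowance for deaths scored 100, which would widen the outcome distribution and weaken the correlation with baseline.

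**The case against.** The strongest reply is that the protocol does indicate its effect analysis. The general paragraph of {20a} assigns the primary endpoint to ANCOVA, and the next paragraph gives evaluating the effect of iron as the purpose of the ANCOVA, with β and its interval as the estimate. The unadjusted test can be read as a preliminary description. Test-selection rules are also commonly left to an analysis plan, and {17a} keeps those who analyse the data blinded to allocation.

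Much of this stands. The lean towards ANCOVA is real and makes the repair short. Blinding limits choosing by direction of effect, although P values remain visible. What does not go away is the conflict between sections: an analysis plan that named ANCOVA would still leave {12} promising medians, and nothing in {20a} makes the first test subordinate.

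A reader might infer more than the documents support:

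- **That the stated power belongs to no analysis.** {14} ties it to the unpaired t-test, and it reproduces.
- **That the trial runs at 6% to 8% type I error.** The protocol states no rule that either test wins. Those figures apply only if that reading is adopted, and requiring both to be significant would be conservative.
- **That a 5-point mean difference is a much smaller difference in medians.** With gamma scores, means 12 and 7 give medians 2.75 points apart if the shape is held, but 5.70 points apart if the SD is held at 15. The protocol does not give the shape, so no figure can be relied on.

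**Conclusion.** The inconsistency is established from the text alone. It concerns the trial's sole confirmatory comparison, and no section resolves it. The harm is ambiguity and room for selective reporting; the sample size is not shown to be too small, since ANCOVA would have at least the planned power under the assumptions in the working.

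The size depends on how the gap would be filled. If either analysis could be claimed, type I error would be about 6.4% to 8.3% over assumed correlations of 0.3 to 0.7. With one named analysis it returns to about 5%. The point should be settled before unblinding.

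**What to change.** - **{20a}:** name the ANCOVA as the single confirmatory analysis at two-sided 5%, adjusted for baseline WHODAS, baseline Hb and the two stratification factors (centre and type of surgery). The effect measure is the adjusted mean difference with its 95% confidence interval. Delete the distribution-dependent choice, and label the unadjusted t-test or Wilcoxon test, whichever is kept, as supportive.
- **{12}:** replace the difference in medians with the matching adjusted mean difference.
- **{14}:** keep 142 per arm, and say that the t-test calculation is a conservative basis for the ANCOVA: about 84%, 90% and 98% power at assumed correlations of 0.3, 0.5 and 0.7, not allowing for deaths scored 100.

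The cost is wording in three sections, recorded as an amendment. No patients or extra data are needed. The downside is that the investigators give up the freedom to choose the test after seeing the data.

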### Trial design {8}

This is a randomized placebo-controlled double-blind multi-centre superiority trial with two parallel groups in which IVI is compared to a placebo. The patient allocation ratio is 1:1, stratified by centre and type of cardiac surgery.

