## Methods: participants, interventions and outcomes

### Study setting {9}

This study is initiated in two large community hospitals in the Netherlands (St. Antonius Hospital, Nieuwegein, and Amphia Hospital, Breda). Patients are preoperatively recruited and eligible if they meet the criteria as defined below.

Primary inclusion criteria:

In order to be eligible to participate in this study, a subject must meet all of the following criteria:Age ≥ 70 years and mentally competentElective AVR or CABG surgery (including AVR or CABG surgery combined with rhythm surgery, i.e. maze, pulmonary vein isolation and left atrial appendage closure)

Primary exclusion criteria:

A potential subject who meets any of the following criteria will be excluded from participation in this study:Medical history of iron overload/haemochromatosisMedical history of liver cirrhosis or ALT/AST serum concentrations > 3 times the reference value (female patients: ALT > 120, AST > 105 U/L, male patients: ALT > 150, AST > 135 U/L)Renal failure (eGFR < 15 mL/min/1.73 m^2^)Recent treatment with IVI (< 12 weeks prior to surgery date)Serious or severe allergic reaction to IVI in medical historySevere asthma or eczema in medical history (atopic constitution)

Definitive eligibility is assessed at postoperative day (POD) 1 based on the criteria below:

Moderate postoperative IDA, defined as:Hb between 85 and 110 g/L(TSAT) < 20%Meeting the criteria for discharge from ICU to general ward (uncomplicated surgery), defined as:No inotropic agents or ventilation at the time of final inclusion (POD 1)Expected discharge to a general ward at POD 1

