### Methods for additional analyses (e.g. subgroup analyses) {20b}

For sensitivity analysis, baseline differences between treatment arms are assessed with the independent Student’s *t* test or Wilcoxon rank sum test and if needed, multivariable analyses will be used to adjust for possible imbalances. Subgroup analysis will be performed for CABG and AVR surgery patients separately.

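### The primary ANCOVA omits the two randomisation strata (a small, conservative loss of precision), and the sensitivity model picks its covariates by testing baseline differences

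*Protocol article*

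**What the plan says.** Trial design {8} states: "The patient allocation ratio is 1:1, stratified by centre and type of cardiac surgery". Sequence generation {16a} repeats both factors, as hospital site and AVR versus CABG. Study setting {9} says: "This study is initiated in two large community hospitals in the Netherlands". Two sites and two procedures give four strata.

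Statistical methods {20a} first compares 90-day WHODAS-12 between arms with a t test or Wilcoxon test. To evaluate the effect of iron, "an ANCOVA analysis will be performed with an adjustment for baseline Hb levels and WHODAS-12 scores". Neither stratum is among the named covariates, and the two-group tests do not use them.

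Additional analyses {20b} has the only other relevant text. It begins "For sensitivity analysis, baseline differences between treatment arms are assessed with the independent" t test or the Wilcoxon test, and adds that "if needed, multivariable analyses will be used to adjust for possible imbalances". It names no covariates and no threshold. Type of surgery then appears once more: "Subgroup analysis will be performed for CABG and AVR surgery patients separately". Centre appears nowhere in the statistical methods.

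**The concern.** Blocked randomisation within strata forces the arms to be nearly balanced on centre and surgery type. Differences between strata then hardly contribute to the true sampling variation of the treatment estimate. A model without the strata still counts those differences as noise, so its standard error is too large, its interval too wide and its p-value too big. The sponsor thought these factors important enough to stratify on, and the stated analysis does not collect the precision that this can yield.

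The baseline tests are a separate matter. In a properly randomised trial, any significant baseline difference is a chance finding. Selecting covariates by the size of that difference ignores whether they predict 90-day disability, and the model is not known until the data are seen. A sensitivity analysis built in this way is a weak check on the primary result.

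Neither point depends on detail that a separate analysis plan would normally supply. The article itself names the primary covariates and the baseline-testing procedure.

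**Working it through.** **Plan's own figure.** Inputs from Sample size {14}: difference 5 points, SD 15, two-sided 5%, power 80%. The article says that "a two-sided significance level of 5% and a power of 80% with equal allocation to two arms would require 142 patients per treatment group".

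- n per group = 2 × 15² × (1.960 + 0.842)² / 5² = 141.3, rounded up to 142. The t-distribution solution is 142.25. The 142 is reproduced.
- Total: 284 / 0.9 = 316, or 284 × 1.1 = 313. The stated 310 is within about 2% of either, and the gap has no bearing here.

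**Omitting the strata.** Let R² be the share of the residual variance, after baseline WHODAS-12 and Hb, that the strata explain. The documents give no value, so 0.01 to 0.10 is assumed, with 0.20 as an outer case. Blocking is also assumed. The SD of 15 is used as the residual SD for simplicity.

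- The test statistic without strata has standard deviation f = √(1 − R²) instead of 1.
- Actual size = 2 × [1 − Φ(1.96 / f)].
- Expected statistic with no correction: 5 / (15 × √(2/142)) = 2.809.
- Power without strata = Φ((2.809 − 1.96) / f).
- Power with strata = Φ(2.809 / f − 1.96).
- For scale, one evenly split two-level factor explaining R² implies a gap between its levels of 2 × 15 × √R².

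| R² (assumed) | Implied gap, points | Actual size | Power without strata | Power with strata | Points forgone |
|---|---|---|---|---|---|
| 0.01 | 3.0 | 4.9% | 80.3% | 80.6% | 0.3 |
| 0.02 | 4.2 | 4.8% | 80.4% | 81.0% | 0.5 |
| 0.05 | 6.7 | 4.4% | 80.8% | 82.2% | 1.4 |
| 0.10 | 9.5 | 3.9% | 81.5% | 84.2% | 2.7 |
| 0.20 | 13.4 | 2.8% | 82.9% | 88.1% | 5.2 |

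The last column uses unrounded values.

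A simulation under the null (284 patients, four strata, assumed blocks of 4, 6,000 runs, Monte Carlo standard error about 0.3 points) gave sizes without strata of 4.6%, 4.6%, 4.3% and 2.9% for R² of 0.02, 0.05, 0.10 and 0.20. With strata in the model they were 4.8%, 5.2%, 5.7% and 5.2%. The direction and approximate size agree with the formula. The 5.7% is about 2.5 standard errors above 5% and shows no trend with R².

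**Testing baseline differences.** The article gives neither the number of variables nor the trigger. With k independent variables and an assumed 5% trigger, the chance of at least one flag under correct randomisation is 1 − 0.95^k: 23% for k = 5, 34% for 8, 40% for 10 and 64% for 20.

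In the same simulation, eight covariates together explaining 10% of the residual variance were added, with R² = 0.05. Choosing among them by test gave a size of 4.4% and power of 80.5%. A prespecified model with the strata and all eight gave 84.4%, and the model with neither gave 80.2%. Choosing by test therefore recovered almost none of the available gain. All of these inputs are assumed.

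**The case against.** The strongest reply is that little is at stake, and most of it stands.

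- **No false-positive risk.** Omitting the strata lowers the actual size. A reader might infer miscalibration that threatens validity, but the error runs only in the conservative direction.
- **The plan is not underpowered because of this.** At 142 per group, power without strata is still 80% or more in every row of the table. What is lost is spare efficiency, measured against a better model.
- **The larger effects need strong strata.** An R² of 0.10 corresponds to a gap of about 9.5 points for a single evenly split factor, nearly twice the 5-point target, where Sample size {14} gives a mean of 12. Baseline WHODAS-12 and Hb may already absorb part of what the strata would explain.
- **Blocking is not stated.** The article says that allocation is stratified and describes no blocks. Without blocking, balance is not forced and the size argument falls away, although adjustment could still gain precision.
- **The data-driven model is a sensitivity analysis.** A reader might infer that the primary covariates are chosen by test. They are not: {20a} fixes them in advance.
- **Secondary models.** A reader might extend the criticism to the secondary ANCOVA, logistic and Poisson models. The article names no covariates for those, so nothing is misstated. In a logistic model, adding covariates also changes the odds ratio being estimated from marginal to conditional.

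What the reply does not answer is that the stated primary covariate set leaves out two factors already recorded at randomisation, at almost no saving, and that testing baseline differences is a poor way to build any model.

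**Conclusion.** The point holds as a modest, inexpensive improvement. The stated primary ANCOVA omits both stratification factors. If the list is blocked and the strata explain 1% to 10% of the residual variance, the nominal 5% test runs at about 4.9% to 3.9%, and about 0.3 to 3 points of power are forgone. The R² range and the blocking are assumptions, and nothing in the article shows where in that range the trial would fall. Validity is not threatened and the planned power is not missed.

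The baseline-testing rule is a separate fault confined to the sensitivity analysis. The 23% to 64% chance of a spurious flag illustrates it for 5 to 20 independent variables at a 5% trigger. It is not a prediction for this trial.

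**What to change.** 1. In {20a}, add centre and type of surgery, coded as used for randomisation, as fixed factors in the primary ANCOVA alongside baseline WHODAS-12 and baseline Hb. State that the treatment coefficient from this model, with its 95% confidence interval, is the estimate of the effect of intravenous iron.
2. In {20b}, delete the t and Wilcoxon tests of baseline differences and the conditional adjustment. If a further adjusted sensitivity model is wanted, name its covariates before unblinding, chosen for expected prognostic value from variables already collected. The choice belongs to the investigators; the article gives no basis for prescribing particular extra variables.

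Cost: wording, and about two degrees of freedom with two centres and two procedures. With 284 analysed patients, residual degrees of freedom go from 280 to 278. Both factors are known at randomisation, so no new data are needed, and the sample size does not change.
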